#### Suicide stigma

The stigma (eight items) and glorification and normalisation (four items) subscales from the Stigma of Suicide Scale-Short Form^25^ will be used to assess attitudes towards suicide. Participants rate their level of agreement with 1–2 word descriptors of a person who dies by suicide on a 5-point Likert scale ranging from 1 (strongly disagree) to 5 (strongly agree). Item scores for each subscale are summed to generate a total score ranging from 8 to 40 for the stigma subscale and 4–20 for the glorification and normalisation subscale. Higher scores on each subscale indicate higher levels of suicide stigma and the glorification and normalisation of suicide. The stigma (α=0.89) and glorification and normalisation (α=0.82) subscales have shown high internal consistency.^26^

#### Help-seeking attitudes

Help-seeking attitudes will be assessed using a modified version of the 10-item Attitude Towards Seeking Psychological Professional Help Scale-Short Form (ATSPPH-SF).^27 28^ Seven scale items have been adapted to elicit a parent’s attitudes towards help-seeking for their child (eg, ‘I would want to get psychological help if my child was worried or upset for a long period of time’). Each item is rated on a 4-point Likert scale ranging from 0 (disagree) to 3 (agree). Five items are reverse-scored prior to summing item scores to generate a total scale score ranging from 0 to 30. Higher scores indicate more positive attitudes towards seeking professional help. Previous research using the ATSPPH-SF has reported high internal consistency (α=0.84).^29^

#### Barriers to help-seeking

To assess parent perceptions of modifiable barriers to help-seeking, a list of 11 barriers was developed based on items from the Barriers to Access to Care Evaluation,^30^ and previous research investigating help-seeking barriers.^29 31^ Example items include ‘I would prefer to work it out as a family’ and ‘Seeking help might impact my child’s future prospects’. Each item is responded to on a 5-point scale ranging from 1 (not true for me) to 5 (true for me). Item scores are summed to form a total scale score ranging from 11 to 55, with higher scores indicating higher perceived barriers to help-seeking.

#### Help-seeking intentions

The General Help-Seeking Questionnaire^32^ will be used to measure help-seeking intentions for a child’s personal or emotional problems. Intentions to seek help from 13 different formal and informal sources (eg, intimate partner, friend, general practitioner and teacher) are assessed on a 7-point Likert scale ranging from 1 (extremely unlikely) to 7 (extremely likely). An additional item will also assess the likelihood of not seeking help from anyone.

#### Psychological distress

The Distress Questionnaire 5^33^ will be used to assess participants’ general psychological distress. The scale investigates psychological distress in the last 30 days, with items rated on a scale from 1 (never) to 5 (always). Item scores are summed to generate a total score ranging from 5 to 25, with higher scores reflecting greater psychological distress. Internal consistency for this scale is high (α=0.86).^33^

#### Resource satisfaction, acceptability and engagement

Among intervention condition participants, the level of engagement with the resources will be assessed at postintervention using resource backend data (eg, logins and completion), as well as self-report data on the number of times the resource was accessed, time spent on the resource, if participants downloaded any information sheets and whether they shared the resource content with anyone. At follow-up, participants will be asked if they accessed the resource over the previous 12-week period and, if so, which sections and, why.

Satisfaction and acceptability of the mental health and suicide gatekeeper resource will also be assessed at postintervention using a satisfaction measure adapted from a previous study.^34^ Open-ended questions at postintervention will also be used to identify what participants liked most and least about the resource, what they found to be most useful and important, the likelihood of recommending the resource to other parents and possible resource changes or additions. A list of seven potential barriers to accessing the resource will also be presented to participants, who will be asked to select any relevant barriers, with a free-text response available to nominate other barriers.^35^

Semistructured interviews of approximately 60 min will also be conducted with 15–20 intervention-condition participants to further explore motivations to use the resource, what parts of the resource were most and least helpful, if they had shared their learning with anyone and possible resource refinements and dissemination pathways. We believe this number will be sufficient to explore the perspectives of parents with a range of mental health experiences.

#### Demographic information

At the preintervention assessment, participants will be asked to provide their age, gender (female, male, non-binary and use different terms), language spoken at home (English only, English and another language and another language only), state or territory of residence, residential location (metropolitan, regional, rural or remote), employment status, level of education, relationship status, number of children, number of primary-school-aged versus secondary-school-aged children, previous qualifications or training in mental health and mental health history of the parent.

#### Child mental health

At preintervention and to assist with randomisation, participants will be asked whether a child in their care has experienced a mental health problem and, if yes, whether their child received treatment. At the preintervention and follow-up assessments, participants will be asked whether they have been concerned about their child’s mental health in the last 3 months. Depending on the response, participants may be asked several follow-up questions about whether and why they have, or have not, spoken to their child about this concern, whether they supported their child in seeking help, what motivated them to take (or not take) action and who they sought help from. Participants will also be asked whether they have used any resources to help with their child’s mental health in the last 3 months and to specify which resources they have used.

### Sample size and power calculations

The calculation of the required sample size was based on detecting a moderate postintervention effect size (d=0.4) for change in self-efficacy between the intervention and waitlist control conditions. Power was set at 0.9, α=0.05 (two-tailed) and a correlation of 0.5 was assumed between preintervention and endpoint scores. Accommodating potential attrition rates between 30% and 50%, the target sample size is 380 participants (190 per condition).

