#### Intervention effects

Statistical analysis of continuous measures will be undertaken on an intent-to-treat basis, including all participants randomised regardless of intervention completion or withdrawal from the study. Mixed-model repeated measures analysis of variance will be used, with measurement occasion as a within-groups factor and condition as a between-groups factor. This approach yields unbiased estimates of intervention effects under the assumption that data is missing completely at random or at random and will allow the inclusion of participants with missing data without using biased techniques, such as the last observation carried forward.^36^ For any dichotomous outcomes, a comparable binary mixed modelling approach^37^ will be used. Cohen’s d effect sizes will be calculated for each time point. If efficacy is demonstrated, exploration of potential mediators and moderators of response, such as child’s age, child’s mental health, participant gender and intervention completion, will be explored separately using three-way interaction terms and stratified models.

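### The target of 380 is the 30% attrition figure and does not give the stated 90% power across the 30–50% attrition range it is said to accommodate

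*Protocol article*

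**What the plan says.** Under 'Sample size and power calculations', the Protocol article bases the calculation on "detecting a moderate postintervention effect size (d=0.4) for change in self-efficacy between the intervention and waitlist control conditions". The other inputs are: "Power was set at 0.9, α=0.05 (two-tailed) and a correlation of 0.5 was assumed between preintervention and endpoint scores". The result follows directly: "Accommodating potential attrition rates between 30% and 50%, the target sample size is 380 participants (190 per condition". The section does not say that power falls anywhere within that attrition range.

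Under 'Intervention effects', the analysis is a repeated-measures mixed model on everyone randomised, "with measurement occasion as a within-groups factor and condition as a between-groups factor". Self-efficacy is measured on three occasions, including preintervention (Table 1), and no baseline covariate is mentioned. The Abstract describes the primary comparison as one of change between arms. 'Aims and hypotheses' places the primary endpoint at postintervention.

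**The concern.** One sample size cannot meet the same power target at both 30% and 50% attrition unless it was set for the upper figure. If 380 was set for the lower figure, the sentence claims a power that the design lacks over much of the range that the plan itself treats as possible. A null primary result after heavy attrition would then be read against 90% power when the true figure is lower. The article prints every input and the resulting number, so this can be checked directly. It is not a matter of detail left to a fuller document.

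**Working it through.** **Inputs.** From 'Sample size and power calculations': d = 0.4 for change, power 0.90, two-sided alpha 0.05, correlation r = 0.5, attrition 30% to 50%, N = 190 per arm. From 'Randomisation': 1:1 allocation. Scores are scaled to SD = 1.

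**Step 1: reproduce 380.** The SD of change is √(2(1 − r)) = √(2 × 0.5) = 1.0. The normal approximation gives n = 2(1.960 + 1.282)²/0.4² ≈ 131.4, so 132 per arm. The exact two-sample t calculation gives 133.

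- 30% attrition: 133/0.70 = 190 per arm, 380 in total. This matches the plan.
- 40% attrition: 133/0.60 = 221.7, so 222 per arm, 444 in total.
- 50% attrition: 133/0.50 = 266 per arm, 532 in total.

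So 380 is the 30% attrition figure.

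**Step 2: power with 190 randomised per arm.** Let m be the number per arm with postintervention data: 133, 114 and 95 at 30%, 40% and 50% attrition. The variance of the change estimate in one arm is:

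- Completer change score: 1/m.
- Planned mixed model, baseline as an occasion and dropouts' baselines kept: (1 − r²)/m + (1 − r)²/N = 0.75/m + 0.25/190.
- Baseline-adjusted (ANCOVA), not described in the article: (1 − r²)/m = 0.75/m.

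Power is Φ(0.4/√(2 × variance) − 1.960). For the mixed model at 50% attrition:

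- Variance = 0.75/95 + 0.25/190 = 0.00789 + 0.00132 = 0.00921.
- √(2 × 0.00921) = 0.1357, and 0.4/0.1357 = 2.947.
- Φ(2.947 − 1.960) = Φ(0.987) = 0.838.

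| Analysis | 30% | 40% | 50% |
|---|---|---|---|
| Planned mixed model | 0.924 | 0.889 | 0.838 |
| Completer change score (t) | 0.901 | 0.852 | 0.783 |
| Baseline-adjusted (t) | 0.963 | 0.935 | 0.886 |

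Under the planned model, power is 0.901 at 37% attrition and 0.897 at 38%, so 90% holds to about 37%. A simulation of 20,000 trials with 50% missing completely at random gave 0.832 for the mixed-model contrast and 0.785 for completer change, in line with the formulas.

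**Step 3: effect detectable with 90% power at 50% attrition.** This is 3.242 × √(2 × variance):

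- Planned model: 3.242 × 0.1357 = 0.44.
- Completer change: 3.242 × √(2/95) = 0.47.
- Baseline-adjusted: 0.47 × √0.75 = 0.41.

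For 90% power at d = 0.4 with 50% attrition, the total randomised would be about 460 (planned model), 528 to 532 (completer change) or 396 to 400 (baseline-adjusted).

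**The case against.** **The range may span two assessments.** The calculation is for the postintervention effect, and 'Attrition and preintervention comparisons' treats attrition at postintervention and at 12 weeks separately. If 30% was meant for the primary endpoint and 50% for follow-up, 380 is correctly sized for the primary endpoint. This is possible, but the text does not say it: the whole range is attached to a calculation for the postintervention effect. The sentence would need rewording on this reading too.

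**The planned model does better than the completer calculation.** This stands. A reader might infer from step 1 that 90% power holds only at exactly 30% attrition, or that power under the planned analysis falls to 0.78. Neither is supported: 0.78 belongs to a completer t-test that the article does not plan, and under the planned model 90% holds to about 37%. A reader might also infer that the type II error roughly doubles at 40–50% attrition. Under the planned model it is 0.11 at 40% and 0.16 at 50%, against 0.10 stated.

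**Other routes do not restore 90% at the upper end.** A baseline-adjusted analysis comes close (0.89) but is not described. Nor does 380 come out as its sample size (284 to 286 at 30% attrition, 396 to 400 at 50%). The 12-week scores of people who missed postintervention could recover a little. As an upper bound, suppose everyone answers at 12 weeks and every pair of occasions correlates 0.5. The residual variance falls to 1 − 2(0.25)/1.5 = 0.667. The per-arm variance is then 0.667/95 + 0.333/190 = 0.00877, and power is Φ(0.4/0.1325 − 1.960) ≈ 0.86.

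**Conclusion.** Wrong as written; should-fix. The target of 380 is the change-score requirement at 30% attrition. It does not deliver 90% power throughout the 30–50% range by any of the analyses considered. Under the planned mixed model the shortfall begins at about 37% attrition, is about one percentage point at 40%, and reaches about six points at 50% (power about 0.84, detectable d about 0.44 rather than 0.40).

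The figures assume equal attrition in both arms, data missing at random, the stated correlation of 0.5 and, in the table, no recovery from 12-week responses. The documents do not support the stronger conclusion that the trial is badly underpowered or must enrol more. The 50% figure is the extreme of a range described as potential, and the design keeps a fair level of power there.

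**What to change.** Restate the last sentence of 'Sample size and power calculations' along these lines: *380 participants (190 per condition) give 90% power for d=0.4 with 30% attrition at postintervention on the change-score calculation (to about 37% under the planned mixed model); at 50% attrition, power under the planned model is about 84% (detectable d about 0.44).* State also which assessment the 30–50% range applies to: postintervention, the 12-week follow-up, or both.

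This needs no added participants and no change to the analysis or conduct. The cost is a slightly less favourable stated power at the upper end of attrition.

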### Data analysis plan

#### Attrition and preintervention comparisons

Logistic regression analyses will be conducted to identify significant predictors of attrition at postintervention and 12-week follow-up. Univariate mixed effect models will be used to identify any differences between the intervention and waitlist control conditions at preintervention.

#### Intervention effects

Statistical analysis of continuous measures will be undertaken on an intent-to-treat basis, including all participants randomised regardless of intervention completion or withdrawal from the study. Mixed-model repeated measures analysis of variance will be used, with measurement occasion as a within-groups factor and condition as a between-groups factor. This approach yields unbiased estimates of intervention effects under the assumption that data is missing completely at random or at random and will allow the inclusion of participants with missing data without using biased techniques, such as the last observation carried forward.^36^ For any dichotomous outcomes, a comparable binary mixed modelling approach^37^ will be used. Cohen’s d effect sizes will be calculated for each time point. If efficacy is demonstrated, exploration of potential mediators and moderators of response, such as child’s age, child’s mental health, participant gender and intervention completion, will be explored separately using three-way interaction terms and stratified models.

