**Methods and analysis:**

A two-arm randomised controlled trial will compare an online mental health and suicide gatekeeper resource for parents and caregivers to a waitlist control. Australian parents of children aged 5–17 years recruited through social media and community advertising will participate in an online trial. Participants randomised to the intervention condition will be emailed the resource to work through at their own pace. The resource consists of three sections providing parents and caregivers with confidence, knowledge and skills to recognise and respond to mental health problems and suicide risk in their child, as well as support them in accessing professional help. The primary outcome measure is self-efficacy to recognise, respond and provide support for mental health problems and suicide risk, while secondary outcomes include perceived knowledge, stigma, literacy, help-seeking attitudes, intentions and barriers. Data will be collected at preintervention, postintervention (4 weeks after accessing the resource) and 12-week follow-up. Primary analyses will compare changes in self-efficacy in the intervention condition relative to the waitlist control using mixed-model repeated measures analyses.

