### Study design

A two-arm RCT with an intervention condition (mental health and suicide gatekeeper resource) and a waitlist control condition will be conducted. Outcome measures will be administered on three occasions: preintervention, postintervention (4 weeks after receiving access to the intervention) and 12-week follow-up.

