### Randomisation

After consenting to participate in the trial and completing the preintervention survey, each participant will be individually randomised to the intervention or waitlist control condition. Stratified randomisation will be conducted by an independent statistician who is not involved in the day-to-day management of the trial according to ICH guidelines,^17^ using a computerised random number generator with 1:1 allocation to the intervention and waitlist control conditions using predetermined block sizes of 6. Randomisation will be stratified by participant gender (female vs male, non-binary, use different terms, prefer not to answer) and child with the experience of a mental health problem (yes vs no) to ensure an even balance of mothers and fathers and pre-existing child mental health exposure across conditions.

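### The primary model estimates a difference in change and makes no use of the equal baseline means that randomisation guarantees in expectation; a common-baseline constraint would cut the variance by 14–19% at no cost

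*Protocol article*

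**What the plan says.** The Intervention effects section names the model: "Mixed-model repeated measures analysis of variance will be used, with measurement occasion as a within-groups factor and condition as a between-groups factor". Study design makes preintervention one of the occasions: "Outcome measures will be administered on three occasions: preintervention, postintervention (4 weeks after receiving access to the intervention) and 12-week follow-up". The abstract gives the comparison: "Primary analyses will compare changes in self-efficacy in the intervention condition relative to the waitlist control using mixed-model repeated measures analyses". The sample size rests on "detecting a moderate postintervention effect size (d=0.4) for change in self-efficacy between the intervention and waitlist control conditions", with these further inputs: "Power was set at 0.9, α=0.05 (two-tailed) and a correlation of 0.5 was assumed between preintervention and endpoint scores". The target is 380 participants, 190 per condition, for attrition of 30% to 50%.

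Under Randomisation, allocation follows consent and completion of the preintervention survey. The section on attrition and preintervention comparisons tests for baseline differences between conditions in separate models. Nowhere does the article give the primary model a baseline covariate or a common preintervention mean.

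**The concern.** When preintervention is an ordinary occasion and condition may differ at every occasion, the model estimates a baseline difference between conditions and subtracts it from the postintervention difference. Here that baseline difference is known to be zero in expectation, because the survey precedes randomisation. Estimating it adds noise to the primary contrast and removes no bias.

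What is at stake is precision at the primary endpoint. The trial expects to lose 30% to 50% of its participants, so analysed numbers are scarce there, and the lost precision could be recovered without recruiting anyone.

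**Working it through.** **Inputs.** From Sample size and power calculations: d = 0.4, two-sided α = 0.05, power 0.90, r = 0.5, N = 190 randomised per arm, attrition 30% to 50%. From Randomisation: "1:1 allocation to the intervention and waitlist control conditions". Assumptions made here: SD 1 at each occasion, the same attrition in both arms, baseline complete, normal approximation.

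**Reproducing the plan's figure.** The variance of a change score is 2(1 − r) = 2 × 0.5 = 1.
- Change score: n = 2 × [(1.960 + 1.282)/0.4]² = 131.4, so 132 per arm. At 30% attrition, 132/0.70 gives 189 per arm, 378 in total, which matches 380. At 50% the total is 528.
- Baseline-adjusted: the variance is 1 − r² = 0.75, so 99 per arm, giving 284 in total at 30% and 396 at 50%. Neither matches 380.

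The match supports reading the design as one on change. It does not prove it: an adjusted calculation would give 380 at about 48% attrition (1 − 198/380 = 0.479). The reading rests mainly on the text, which refers to change in both the abstract and the sample-size section.

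**Variance of the postintervention contrast, per arm**, with n_c the number analysed at postintervention:
- Planned model, with dropouts' baselines kept: (1 − r²)/n_c + (1 − r)²/N
- Common baseline mean: (1 − r²)/n_c

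The second term of the planned model, 0.25/190 = 0.00132 at r = 0.5, is the price of estimating the baseline difference. Power is Φ(0.4/√(2v) − 1.96), with v the per-arm variance.

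| Attrition | n_c | Planned v | Constrained v | Cut | Power, planned | Power, constrained |
|---|---|---|---|---|---|---|
| 0% | 190 | 0.00526 | 0.00395 | 25% | 0.974 | 0.994 |
| 30% | 133 | 0.00564 + 0.00132 = 0.00696 | 0.00564 | 19% | 0.924 | 0.965 |
| 50% | 95 | 0.00789 + 0.00132 = 0.00921 | 0.00789 | 14% | 0.838 | 0.889 |

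A generalised-least-squares calculation over all three occasions, assuming equal correlations of 0.5, gave the same variance ratios (0.75, 0.811, 0.857) and the same power.

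**Other correlations.** Variance cut from the same formulas:

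| r | 30% attrition | 50% attrition |
|---|---|---|
| 0.3 | 27% | 21% |
| 0.6 | 15% | 11% |
| 0.8 | 7% | 5% |

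**In participants, at 50% attrition and r = 0.5.** If randomised and analysed numbers grow together, 95 × 0.00921/0.00789 ≈ 111, or 16 more per arm. If 190 randomised is held fixed, 0.75/n + 0.00132 = 0.00789 gives n = 114, or 19 more per arm.

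**The case against.** The strongest reply is that nothing here is wrong. Under randomisation, the difference in change and the baseline-adjusted difference have the same expectation. The planned model is standard, and it agrees with a sample size based on change. A reader might infer that the planned estimate is biased; the documents do not support that, and the point concerns efficiency only.

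A second reply is that one sentence in a journal article leaves detail to an analysis plan. It is true that the condition-by-occasion term is not written out. But the section plans third-order interactions for moderators, which presuppose that term, and the abstract, Study design and sample-size sections all point to change from preintervention. This is a method the article states, so the point is not about a missing detail.

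Third, the practical gain is bounded. At 30% attrition the planned model already exceeds 0.90 power. A reader might quote the 25% reduction from comparing 1 with 0.75, but that needs complete data or a completers-only comparison. The planned model keeps dropouts' baselines, so 14–19% is the figure for the planned attrition. A reader might also infer that the constraint restores 0.90 power at 50% attrition; it reaches 0.889. What remains of that shortfall belongs to the sample size.

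**Conclusion.** The point holds as a loss of efficiency in a valid analysis. At r = 0.5 and the planned attrition, the stated model gives up 14–19% of the variance of the primary contrast, or 4 to 5 points of power. At 50% attrition a common baseline mean recovers 0.051 of the 0.062 by which the planned model misses 0.90, which is worth about 16–19 analysed participants per arm.

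The size depends on the correlation. It is larger if r is below 0.5 and only about 5–7% at r = 0.8. It also rests on the condition-by-occasion reading of the model and on equal attrition in the two arms. The direction depends only on baseline being measured before randomisation and on the correlation being below 1.

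**What to change.** State the primary model as a constrained longitudinal analysis of all three occasions: one preintervention mean common to both conditions, condition-by-occasion terms at postintervention and 12 weeks only, and an unstructured covariance. Name the condition difference at postintervention as the primary test. This suits the stated hypothesis, which concerns the level of self-efficacy at that occasion. Every randomised participant with a baseline stays in the likelihood, as the intention-to-treat wording of the section intends.

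A mixed model of the two later occasions, with baseline self-efficacy as a covariate, gives nearly the same precision. It omits participants who have baseline data only, so it fits that wording less well.

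The cost is a change of analysis wording. No new data, visits or participants are needed. The choice should be recorded before outcomes are examined by condition, so that it cannot appear to depend on the results.

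### The stated primary model does not name the two randomisation strata; adding them with occasion interactions is a small, nearly free gain in precision

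*Protocol article*

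**What the plan says.** The Randomisation section of the protocol article states: "Randomisation will be stratified by participant gender" (female against all other responses) and by child mental-health experience (yes or no). Allocation is 1:1, "using predetermined block sizes of 6". The stated purpose is "to ensure an even balance of mothers and fathers and pre-existing child mental health exposure across conditions".

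The Intervention effects section describes the primary model as a mixed-model repeated measures analysis of variance, "with measurement occasion as a within-groups factor and condition as a between-groups factor". No other model term is named. Later in the same paragraph, gender and the child's mental health are listed among possible moderators, to be explored through three-way interactions and stratified models if the resource proves efficacious.

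The abstract fixes the target of the analysis: "Primary analyses will compare changes in self-efficacy in the intervention condition relative to the waitlist control". The sample size section also refers to change in self-efficacy.

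**The concern.** Blocked randomisation within strata removes between-stratum variation from the sampling error of the treatment comparison. A model without the strata leaves that variation in its residual. It then reports a standard error larger than the true one, gives intervals that are wider than they need to be, and rejects a true null less often than 5% of the time. The protocol builds the balance into the design, and the model it states does not use it.

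Missing data give a second, weaker reason. The article plans for 30–50% attrition and relies on data being missing at random. In a likelihood analysis that assumption is conditional on what the model contains. If dropout differs by stratum, the assumption is more plausible with the strata in the model. Nothing in the article shows that dropout does differ in this way.

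**Working it through.** **Inputs from the article.** d = 0.4 for change, two-sided α = 0.05, power 0.90, pre–post correlation 0.5, attrition 30–50%, target 380 (190 per arm), blocks of 6, 1:1 allocation.

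**Assumed inputs.** The share of change variance explained by the strata (R²) is not given. I take 0–10% as the working range and show 20% as an outer case. For the simulation, 85% of participants are female and 50% have a child with mental-health experience.

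**Step 1: the article's sample size.** The SD of change is √(2(1 − 0.5)) = 1. Then n per arm = 2(1.960 + 1.282)²/0.4² = 131.3, so 132. Dividing by 0.7 gives 189 per arm, or 378 in total. With the t distribution, n = 133 and 133/0.7 = 190 per arm, or 380. The stated target is reproduced at 30% attrition. The point made here does not change it.

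**Step 2: what omission does in principle.** With exact balance, the unadjusted model reports √(2/n), while the true standard error is √(2(1 − R²)/n).

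- Relative reduction from adjustment: 1 − √(1 − R²).
- Type I error of the unadjusted test: 2[1 − Φ(1.96/√(1 − R²))], which is 0.044 at R² = 5% and 0.039 at R² = 10%.

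These are limits for exact balance, that is, without attrition.

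**Step 3: simulation.** Stratified blocks of 6, N = 380, 4,000 runs per setting, condition effect on change with and without the two strata. Monte Carlo error on a 5% rate is √(0.05 × 0.95/4000) = 0.003.

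| R² for change | SE reduction (formula) | Type I error, unadjusted, no attrition | Type I error, unadjusted, 40% attrition | Power, unadjusted, 40% attrition | Power, adjusted, 40% attrition |
|---|---|---|---|---|---|
| 0% | 0% | 0.052 | 0.047 | 0.846 | 0.845 |
| 2% | 1.0% | 0.054 | 0.045 | 0.849 | 0.859 |
| 5% | 2.5% | 0.048 | 0.049 | 0.855 | 0.867 |
| 10% | 5.1% | 0.038 | 0.046 | 0.855 | 0.881 |
| 20% | 10.6% | 0.025 | 0.039 | 0.857 | 0.914 |

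At R² = 10% the unadjusted model reports 0.1025 against a true 0.0964 without attrition, a ratio of 1.06. With 40% attrition it reports 0.1325 against 0.1304, a ratio of 1.02. Attrition loosens the enforced balance, so the mismatch shrinks.

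**Step 4: strata that affect level but not change.** A three-occasion random-intercept model was fitted with stratum effects constant over time. The standard error of condition by occasion, without and with the strata, was 0.1253 and 0.1251 when the strata explain 5% of score variance, and 0.1248 and 0.1237 at 20%. This check had 40 runs per setting, so it rests on the mean model standard errors. There is essentially no loss in this case, and a stratum main effect alone would bring little.

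**The case against.** The strongest reply is that the article condenses a longer plan. Its one sentence on the model gives the two design factors; it neither says that these are all the terms nor excludes covariates. A covariate list often sits in an analysis plan, and none is shown here. This lowers the certainty of the point, and it is why confirmation from the plan would settle it. It does not remove the point: the article does state a model, and it gives these two variables a different, conditional role.

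It is also fair to say that the article gives balance as the purpose of stratification, and does not claim that gender or child mental-health experience predicts change in self-efficacy. It expects fathers to be under-represented, which limits how much variance the gender stratum can explain. Both objections stand, and the working range for R² therefore starts at zero.

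A reader might infer more than the documents support:

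- **That intervals are too wide for every continuous outcome.** This needs strata that predict change in each outcome, and no figure is given for any.
- **That the true type I error is 3.9–4.4%.** Those values assume no attrition and R² of 5–10%. At 40% attrition and R² = 10% the simulated rate is 0.046; at 5% or less it is nominal within simulation error.
- **That adjustment lifts power from 0.889 to 0.904–0.918.** Those figures take 95 per arm and a residual variance of 0.75(1 − R²), that is, with preintervention score as a covariate. The stated model has the preintervention score as an occasion.
- **That the missing-at-random assumption fails.** The article plans to look for predictors of attrition, but nothing shows that either factor is one.

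**Conclusion.** The point holds as a low-severity matter of efficiency. The design stratifies on two factors that the stated primary model does not name. If they predict change, the unadjusted test is mildly conservative. With R² for change of 0–10% and 40% attrition, the power forgone is about 0 to 0.03 (0.855 against 0.881 at the top of the range), and type I error stays close to 5%. Under randomisation the omission brings no bias and no excess of false positives, and the sample size is unaffected. These sizes rest on the assumed R² and stratum prevalences. If the strata affect only the level of self-efficacy, the loss is close to nil. Greater plausibility of the missing-at-random assumption is a possible further benefit, not a demonstrated one.

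**What to change.** Add both stratification factors, as used in the randomisation, and their interactions with occasion as fixed effects in the primary mixed model and the continuous secondary models. The interactions are essential, because main effects alone leave the change contrast almost untouched. If the analysis plan already specifies this, a sentence of confirmation is enough. Settle it before outcome data are compared by arm, so that no choice between adjusted and unadjusted results remains.

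For binary mixed models, decide this separately: adding covariates changes the conditional effect being estimated, so the plan should say which effect is intended.

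The cost is small. Two binary factors and their interactions with two later occasions add 2 + 2 × 2 = 6 fixed-effect parameters in a trial of 380. Both factors are recorded before randomisation, so no new data are needed.
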